## Abstract

**Background:**

Undercarboxylated osteocalcin (ucOC) increases insulin sensitivity in mice. In humans, data are supportive, but the studies are mostly cross-sectional. Exercise increases whole-body insulin sensitivity, in part via ucOC, while acute glucocorticoid treatment suppresses ucOC in humans and mice.

**Objectives:**

A single dose of prednisolone reduces the rise in ucOC produced by exercise, which partly accounts for the failed increase in insulin sensitivity following exercise.

**Methods:**

Healthy young men (n=12) aged 18 to 40 years will be recruited. Initial assessments will include analysis of fasting blood, body composition, aerobic power (VO_2peak_), and peak heart rate. Participants will then be randomly allocated, double-blind, to a single dose of 20 mg of prednisolone or placebo. The two experimental trials will involve 30 minutes of interval exercise (90%-95% peak heart rate), followed by 3 hours of recovery and 2 hours of euglycaemic- hyperinsulinaemic clamp (insulin clamp). Seven muscle biopsies and blood samples will be obtained at rest, following exercise and post-insulin clamps.

**Results:**

The study is funded by the National Heart Foundation of Australia and Victoria University. Enrollment has already commenced and data collection will be completed in 2016.

**Conclusion:**

If the hypothesis is confirmed, the study will provide novel insights into the potential role of ucOC in insulin sensitivity in human subjects and will elucidate pathways involved in exercise-induced insulin sensitivity.

## Introduction

Insulin resistance is characterized by impaired insulin action in target tissues. Skeletal muscle is a major site of glucose uptake and disposal in response to insulin and skeletal muscle can become insulin resistant in obese individuals and those with type 2 diabetes mellitus (T2DM). In mice, the skeleton is partly involved in determining insulin secretion, insulin sensitivity, and glucose tolerance via the undercarboxylated form of osteocalcin (ucOC) [1,2]. UcOC- deficient mice have insulin resistance and in obese mice recombinant ucOC treatment reduces glucose levels and increases insulin secretion and sensitivity [2,3]. Moreover, recombinant ucOC increases muscle glucose uptake post ex vivo contraction in mice [4].

In humans, ucOC may influence glycemic control but most evidence is based on cross-sectional studies [5,6]. For example, patients with T2DM have lower serum ucOC than controls. A lower serum ucOC is associated with a higher fasting glucose and fat mass, and lower insulin sensitivity [7,8]. This suggests ucOC participates in glucose homeostasis in humans; however, prospective interventional studies are required [9].

Exercise increases insulin sensitivity in nonobese and obese subjects and in patients with T2DM independent of weight loss [10] Even a single bout of exercise increases glucose handling and insulin sensitivity [11]. Acute exercise also increases ucOC, which is associated with improved glycemic control and increased insulin sensitivity post exercise [7,12,13]. Thus, ucOC may contribute to the regulation of insulin sensitivity in humans.

To explore this, we have designed a prospective study aimed at inhibiting the rise in ucOC using a single dose of a glucocorticoid (GC). GC treatment is used regularly as an anti-inflammatory and immunosuppressive agent [14,15]. Long-term GC treatment causes bone loss, obesity, insulin resistance, and T2DM[16]. The detrimental long-term effects of GC on insulin resistance are partly mediated via osteoblasts, the bone cells responsible for the production of ucOC [14,15,17]. The reduction in insulin sensitivity following short-term GC treatment is related to an acute reduction in osteoblastic function and ucOC levels and not to the GC effects on skeletal muscle or liver, at least in mice [17]. As such, we will use a single dose of a GC, prednisolone, as a tool to acutely suppress ucOC and examine the consequent effect on whole-body insulin sensitivity and muscle metabolism, including measuring GC signaling in muscle. The regulation of GC-target genes, glucocorticoid-induced leucine zipper *(Gilz)*[18] and FK506-binding protein 5 *(Fkbp5)*[19] will be analyzed by polymerase chain reaction (PCR) and Western blot from muscle biopsies of humans with and without an acute dose of prednisolone. We hypothesize that the protein levels of these GC-targets will not be altered in the short time frame, even if gene expression is altered. Other studies in mice and humans confirm a 40% to 50% reduction in circulating OC within 12 to 24 hours after the commencement of GC treatment [20]. On the other hand, 5 days of prednisone treatment had minimal effect on muscle protein synthesis, breakdown, mitochondrial function, strength, and resting energy expenditure in men [21]. Thus, evidence from mice and humans indicates that a reduction in serum OC and ucOC following GC treatment occurs prior to muscle atrophy signaling changes in skeletal muscle. We hypothesize that insulin sensitivity will be partly reduced due to changes in insulin signaling proteins subsequent to a reduction in circulating ucOC levels.

No previous research has used GC (prednisolone) as a tool to examine the effect of ucOC on insulin sensitivity post exercise. Thus, the aim of this study is to test the hypothesis that attenuation of the increase in ucOC following exercise by a single dose of prednisolone reduces insulin sensitivity post exercise, as measured by euglycaemic-hyperinsulinaemic clamp, as well as impairing skeletal muscle insulin signaling. We also hypothesize that markers of muscle damage will not be increased by a single dose of prednisolone.

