### Sample Size and Data Analysis

The sample size is based on our previous work where exercise significantly increased ucOC by approximately 6.5% and insulin sensitivity by approximately 35% during a euglycaemic-hyperinsulinaemic clamp (n=11) [7,12]. As such, we estimate that the sample size needed in this cross-over design (power of 80%, alpha=0.05) is 12 individuals.

Descriptive statistics will be used to describe the volunteers’ characteristics as well as the study measurements. Changes from pre-to-post exercise within each trial and between trials will be analyzed by paired *t*-tests. General linear model analysis of the variance will be use to compare multiple time-points within and between interventions. Multilinear regression model will be used to determine associations between selected measurements. All data will be reported as mean ± standard error of mean and all statistical analyses will be conducted at the 95% level of significance ( *P*≤.05).

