A potential limitation of the current study is that GC are known to effect several other organs/tissues and not only osteoblasts. As such, it is plausible that a reduction in insulin sensitivity following acute GC treatment may not be entirely due to the reduction in ucOC. However, in mice the reduction in ucOC and insulin sensitivity occurred prior to the GC-induced effects in muscle, liver, and adipose following short-term GC treatment suggesting that the changes in insulin sensitivity are related to the reduction in ucOC levels and not to the GC effects on skeletal muscle, fat, or liver [17]. Nevertheless, in the current study we will be able to identify if acute GC treatment has immediate effects on GC-target genes ( *gilz, Fkbp5*, fatty acid binding protein 4, hydroxysteroid (11-Beta) dehydrogenase 1, peroxisome proliferator-activated receptor gamma, and CCAAT/enhancer-binding protein alpha), and any detrimental effect on skeletal muscle, as markers of muscle atrophy and degradation will also be measured.

Another limitation is that the current study will investigate young, healthy men rather than patients with T2DM. As such, it will not be possible to generalize the results to this population. Follow-up studies will be required to confirm that changes in ucOC following interventions are related to changes in insulin sensitivity in patients with T2DM.

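### Two hypotheses of no prednisolone effect on muscle are given only difference tests at P ≤ .05 with n=12, and a non-significant result there cannot support them

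*Protocol article*

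**What the plan says.** Two hypotheses in the Introduction predict no effect of prednisolone on muscle:

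- For GILZ and Fkbp5 protein: "We hypothesize that the protein levels of these GC-targets will not be altered in the short time frame, even if gene expression is altered". This is two-sided, since a change in either direction would contradict it.
- For muscle damage: "We also hypothesize that markers of muscle damage will not be increased by a single dose of prednisolone". This is one-sided, since only a rise would contradict it.

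The section on sample size and data analysis names the methods: paired t-tests, a general linear model and multiple linear regression. On the t-tests it says "Changes from pre-to-post exercise within each trial and between trials will be analyzed by paired" t-tests. It then sets one rule for everything: "All data will be reported as mean ± standard error of mean and all statistical analyses will be conducted at the 95% level of significance", given as P ≤ .05.

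On size, the same section says "we estimate that the sample size needed in this cross-over design (power of 80%, alpha=0.05) is 12 individuals". The basis is earlier work on the exercise response of ucOC (about 6.5%) and of insulin sensitivity (about 35%). No muscle measure enters.

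Under Principal Findings, the Discussion concedes that glucocorticoids act on tissues other than bone, so a fall in insulin sensitivity may not be wholly due to ucOC. It answers first with mouse data on timing. It then adds that "we will be able to identify if acute GC treatment has immediate effects on GC-target genes", and extends this to any harmful effect on skeletal muscle.

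**The concern.** A test of zero difference can give evidence that prednisolone changes a marker. It cannot, by failing to reject, give evidence that the marker is unchanged. The plan pairs two hypotheses of no change with difference tests alone, at a sample size chosen for other endpoints.

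What is at stake is the mechanistic reading. Prednisolone is used as a tool to suppress ucOC, and the main rival explanation for lower insulin sensitivity is a direct glucocorticoid effect on muscle. The muscle measurements are this trial's own check on that rival. If they come out non-significant, the reader needs to know how large an effect the data still allow, and neither a P value nor a blanket mean ± SEM states that directly.

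Using SEM for all data is a smaller, related matter. For participant characteristics it describes the precision of a mean and not the spread between men.

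**Working it through.** **Inputs**

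- n = 12, power 80%, alpha 0.05 (Sample Size and Data Analysis). Sidedness is not stated; two-sided is assumed unless noted.
- Expected effects: 6.5% (ucOC) and 35% (insulin sensitivity), both exercise effects (same section).
- SD of the paired difference: not given for any outcome. All effects and margins below are therefore in units of that SD.
- Margin for no effect: none given. Values from 0.5 to 0.9 SD are assumed for illustration.

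**1. The plan's own figure.** N = 12 cannot be reproduced without an SD, but it can be inverted. Power of the paired t-test is P(|T| > t(0.975, 11)), with T noncentral t on 11 df and noncentrality d × √12. Setting this to 0.80 gives d = 0.889. The implied SD of the difference is 6.5/0.889 = 7.3 percentage points for ucOC, or 35/0.889 = 39 points for insulin sensitivity. So 12 men give 80% power for a paired effect of about 0.89 SD, whatever the endpoint.

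**2. How often a real muscle effect would be non-significant at n = 12** (same formula, two-sided 0.05):

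| True effect (SD of paired difference) | Power | Missed |
|---|---|---|
| 0.3 | 0.16 | 84% |
| 0.5 | 0.35 | 65% |
| 0.7 | 0.60 | 40% |
| 0.8 | 0.71 | 29% |
| 0.89 | 0.80 | 20% |

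**3. What a non-significant result leaves open.**

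- 95% CI half-width: t(0.975, 11)/√12 = 2.201/3.464 = 0.64 SD.
- 90% CI half-width: t(0.95, 11)/√12 = 1.796/3.464 = 0.52 SD.

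With an observed difference of exactly zero, the 95% interval still reaches 0.64 SD each way. With a non-significant but non-zero difference, it reaches further on one side.

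**4. What it takes to support the not-altered hypothesis.** Two one-sided tests at 0.05 each are the same as requiring the 90% CI to lie inside ± margin. With a true difference of zero and n = 12, simulation gives power 11% for a margin of 0.5 SD, 66% for 0.8 SD and 80% for 0.90 SD. For 80% power at a margin of 0.5 SD, N would be about 36.

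**5. What it takes to support the not-increased hypothesis.** Only the upper bound matters. At one-sided 0.05, n = 12 and a true difference of zero, power is 49% for a margin of 0.5 SD and 83% for 0.8 SD. This is easier than step 4, and 12 men suffice for the wider margin.

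**6. SEM against SD.** SD/SEM = √12 = 3.46, so for participant characteristics the printed spread would be about 3.5 times too narrow if read as variation between men.

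**The case against.** The strongest reply is that the protocol nowhere says a non-significant muscle result will be taken as proof of no effect. That is correct. A reader might infer it from the pairing of hypotheses and tests, but the text does not state it. The interpretation is hedged: the Introduction speaks of a partial reduction, and the Discussion says only that ucOC is likely to take part.

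Nor do these hypotheses carry the whole specificity argument, as one might conclude. The Discussion rests specificity first on mouse data and brings in the human muscle measurements as an added check. The proteins and genes are secondary or additional measures.

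Three further points stand:

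- The Discussion's sentence about identifying effects on target genes is a claim to detect effects, not to show their absence, and the Introduction allows that gene expression may change. At n=12 there is 80% power near 0.89 SD, so the claim needs a limit on its reach and not deletion.
- The text does not say that SEM will be given per trial. If the paired change is reported as mean ± SEM, that SEM is the precision of the paired difference and a confidence interval follows from it. The SEM criticism is therefore firm only for participant characteristics.
- The 0.5 and 0.7 SD effects are illustrative. Nothing in the document says how large the muscle effects are likely to be.

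It can also be said that margins and intervals belong in an analysis plan that is not shown. That holds for a bare omission. Here the article itself fixes one threshold and one reporting format for all analyses and all data, and that rule does not fit two of its own hypotheses.

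**Conclusion.** The point holds as a mismatch between hypothesis and method for secondary outcomes. Difference tests at P ≤ .05 with 12 men cannot support the hypotheses that GILZ and Fkbp5 protein are unaltered and that damage markers do not rise. They also cannot exclude a moderate direct muscle effect as an alternative to ucOC: an effect of 0.5 SD would be missed about two times in three. The shortfall is larger for the two-sided hypothesis, which needs a margin of about 0.90 SD for 80% power, than for the one-sided one, where 0.8 SD is within reach.

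The results assume a paired t-test on 12 complete pairs, a two-sided alpha for the difference tests, and margins that are not the document's. The documents do not support the stronger conclusion that the plan treats non-significance as proof. The primary comparisons of ucOC and insulin sensitivity are unaffected.

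**What to change.** In the section on sample size and data analysis:

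- Replace the blanket mean ± SEM rule. Report outcomes as the paired prednisolone-placebo difference with its 95% CI, adding a 90% CI for GILZ and Fkbp5 protein and the muscle damage markers. Use SD for participant characteristics.
- Set a margin for these markers before unblinding. Conclude that a protein is not altered only if the 90% CI lies wholly within the margin. Conclude that a damage marker is not increased only if the upper bound of that interval lies below the margin. Otherwise write that an effect is not excluded.

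In the Discussion, keep the statement about identifying glucocorticoid effects, but add that with 12 participants only effects of about 0.9 SD of the paired difference or larger can be identified reliably.

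The cost is wording, the choice of a margin and a few extra columns of output. No participants, biopsies or assays are added. The drawback is that many muscle results will be reported as inconclusive, which is what 12 pairs can support.

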## Methods

### Study Design and Participants

This is designed as a double-blind, randomized controlled, cross-over study. We aim to recruit 12 healthy young men. Volunteers will be recruited via several advertisement strategies including flyers, global emails to staff and students from Victoria University, and Web-based advertisements.

### Criteria

Healthy young men aged 18 to 40 years, body mass index range between 19 and 27 kg/m^2^with fasting blood glucose ≤ 5.6 mmol/L^1^will be recruited for the study. Men with bone disease (such as osteoporosis), metabolic or cardiovascular disease, and/or those who are taking any medication known to affect bone metabolism, insulin secretion, or insulin sensitivity will be excluded. Also, those with a musculoskeletal and/or orthopedic condition (such as severe osteoarthritis) that prevents normal daily function (such as walking) will be excluded. Conversion of ucOC to OC is dependent on vitamin K [22]. As such, volunteers on warfarin therapy or vitamin K supplementation or restriction will be excluded.

### Sample Size and Data Analysis

The sample size is based on our previous work where exercise significantly increased ucOC by approximately 6.5% and insulin sensitivity by approximately 35% during a euglycaemic-hyperinsulinaemic clamp (n=11) [7,12]. As such, we estimate that the sample size needed in this cross-over design (power of 80%, alpha=0.05) is 12 individuals.

Descriptive statistics will be used to describe the volunteers’ characteristics as well as the study measurements. Changes from pre-to-post exercise within each trial and between trials will be analyzed by paired *t*-tests. General linear model analysis of the variance will be use to compare multiple time-points within and between interventions. Multilinear regression model will be used to determine associations between selected measurements. All data will be reported as mean ± standard error of mean and all statistical analyses will be conducted at the 95% level of significance ( *P*≤.05).

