## Discussion

### Principal Findings

In mice, ucOC is a modulator of insulin sensitivity and ucOC treatment reduces the risk for type 2 diabetes [2,3]. In humans, data are supportive but are based on cross-sectional studies. If this study shows that suppression of ucOC with a single dose of prednisolone leads to suppression of insulin sensitivity post exercise, this suggests that ucOC is likely to participate in the modulation of insulin sensitivity in humans.

Insulin resistance is characterized by impaired insulin action in insulin target tissues. However, muscle glucose uptake is normal during and following exercise in patients with type 2 diabetes [31,32]. As such, understanding the mechanism/s behind the insulin sensitizing effect of exercise on muscle and whole-body glucose uptake can open the door for new therapeutic treatments for T2DM. In this study we focus on ucOC as acute exercise increases ucOC and higher ucOC correlate with an improvement in insulin sensitivity and glycemic control after exercise in obese men [7,12,13].

A single dose (10 mg) of prednisone suppresses OC and ucOC, an effect that lasts for at least 12 hours [20]. We hypothesize that prednisolone will attenuate the increase in ucOC in response to exercise and that this will coincide with reduced insulin sensitivity compared with placebo. This design will enable us to examine whether changes in ucOC levels are related to changes in insulin sensitivity in young healthy men. We also aim to determine the fraction of the observed reduction in insulin sensitivity that is modulated by ucOC in humans.

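### The 80% power stated for 12 participants is derived from the exercise effect in earlier work, and is not supported for the prednisolone-placebo contrast that the trial tests

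*Protocol article*

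**What the plan says.** The Sample Size and Data Analysis section takes its inputs from the group's previous studies, references 7 and 12, where "exercise significantly increased ucOC by approximately 6.5% and insulin sensitivity by approximately 35% during a euglycaemic-hyperinsulinaemic clamp (n=11"). It then concludes: "As such, we estimate that the sample size needed in this cross-over design (power of 80%, alpha=0.05) is 12 individuals". It uses no expected difference between prednisolone and placebo.

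The aim in the Introduction is to test whether "attenuation of the increase in ucOC following exercise by a single dose of prednisolone reduces insulin sensitivity post exercise". Principal Findings in the Discussion repeats this as a comparison of treatments: "prednisolone will attenuate the increase in ucOC in response to exercise and that this will coincide with reduced insulin sensitivity compared with placebo". The matching analysis is a paired t-test: "Changes from pre-to-post exercise within each trial and between trials will be analyzed by paired" t-tests.

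Two further places bear on the point:

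- **Population.** Principal Findings cites references 7, 12 and 13 for the statement that "higher ucOC correlate with an improvement in insulin sensitivity and glycemic control after exercise in obese men [7,12,13"]. The Criteria section enrols "Healthy young men aged 18 to 40 years, body mass index range between 19 and 27" kg/m².
- **Clamp timing.** The Intervention section describes one insulin clamp per trial day, after exercise and 3 hours of recovery. No resting or pre-exercise clamp is described.

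Outcomes Measurements names two primary outcomes: the change in serum ucOC, and the change in insulin sensitivity as glucose infusion rate per unit of insulin.

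**The concern.** Participants exercise on both trial days, so the exercise effect is common to the two treatments. What the trial tests is how much of that effect prednisolone removes. If the rise in ucOC is only attenuated, as the article says, the treatment contrast is some fraction of 6.5%. Taking the whole exercise effect as the detectable difference amounts to assuming that prednisolone abolishes it.

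For insulin sensitivity the gap is wider. With one post-exercise clamp on each day, the trial cannot estimate a 35% gain from exercise, and the article gives no other effect size for this outcome.

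The sentence is the only justification given for the size of an invasive study with seven biopsies and two clamps per participant. A reader will take it as 80% power for the main hypothesis, and a null result could be reported as coming from an adequately powered trial when nothing in the article shows that it was.

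**Working it through.** **Inputs from the article:** n = 12, alpha 0.05, power 80%, exercise effects of 6.5% (ucOC) and 35% (insulin sensitivity), earlier n = 11, paired t-test.

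**Assumption:** the test is two-sided; the article does not say.

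**Step 1. What n = 12 implies.** Let dz be the mean paired difference divided by the SD of the paired differences. Power is the probability that a noncentral t variable with 11 degrees of freedom and noncentrality dz × √12 exceeds the 5% two-sided critical value. Setting power to 80% gives dz = 0.889.

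For the exercise effects this implies:

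- ucOC: SD of the change = 6.5 / 0.889 = about 7.3 percentage points.
- Insulin sensitivity: SD of the change = 35 / 0.889 = about 39 percentage points.

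The article states neither SD, so the 12 cannot be reproduced, only back-solved. It is plausible for the exercise effect. If the earlier test was a two-sided paired t-test, significance with 11 people requires dz ≥ 2.228/√11 = 0.672. A result at exactly P = .05 gives 56% power with 12. A result at P = .01 (dz = 0.956) gives 85%. No arithmetic error is shown.

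**Step 2. Move to the tested contrast, ucOC change only.** Assume that the 80% holds for the exercise effect. Let f be the share of the exercise rise that prednisolone removes, and ρ the correlation between a participant's changes on the two days, with equal SDs. Then

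SD of the difference in changes = SD of one change × √(2(1 − ρ))

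dz for the contrast = 0.889 × f / √(2(1 − ρ))

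Example: f = 0.5 and ρ = 0.5 give dz = 0.889 × 0.5 / 1 = 0.444 and power of 29%.

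Power with 12 participants:

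| Share removed | ρ = 0 | ρ = 0.25 | ρ = 0.5 | ρ = 0.75 |
|---|---|---|---|---|
| All (f = 1) | 51% | 63% | 80% | 98% |
| Three quarters (f = 0.75) | 32% | 41% | 56% | 84% |
| Half (f = 0.5) | 17% | 21% | 29% | 51% |

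The SD of the difference exceeds the SD of one change only when ρ is below 0.5. At ρ = 0.5 they are equal, and above it the difference is less variable.

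**Step 3. Insulin sensitivity.** The contrast is one post-exercise clamp against another, a single paired difference. There is no within-day change to difference a second time, so the table does not apply. The open question is the size of the treatment effect and the SD of that one difference.

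**Step 4. Direct suppression.** The Introduction cites a 40% to 50% fall in circulating total OC within 12 to 24 hours of starting a glucocorticoid. That is 40/6.5 = 6.2 to 50/6.5 = 7.7 times the exercise effect. If the tested ucOC contrast were that large, power with 12 would be 93% to 99% even with five times the SD in Step 1.

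**The case against.** The tempting stronger reading is that the trial falls short of 80% power. The article does not support it. It gives neither a treatment difference nor a paired SD, and the scenarios above fall on both sides of 80%. Full attenuation with ρ = 0.5 gives exactly the stated figure, and a higher correlation gives more. The fall in OC cited in the Introduction could mean a treatment effect on ucOC well beyond cancelling a 6.5% rise. The Abstract also speaks of a failed increase in insulin sensitivity, which could be read as complete loss of the exercise gain. All of this stands, and it rules out any claim that the power is not achieved.

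It does not rescue the sentence as written. The sample-size section does not use the glucocorticoid figure, which concerns total OC and says nothing about insulin sensitivity. Suppression already present before exercise may also not show in a comparison of pre-to-post changes, although the planned general linear model across time points could pick it up. The Abstract says only that prednisolone reduces the ucOC rise, and that this partly accounts for the insulin result.

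A reader might also infer that the obese source population makes the power too optimistic. The article gives no direction: nothing in it says that leaner men have a smaller effect or a larger SD. The mismatch means only that the inputs do not transfer without argument.

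Finally, an article may leave the SD to the full protocol, so its absence is no part of this point. The point is that the article does state a basis, and that basis is a different contrast.

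**Conclusion.** The point holds as a failure of justification. The 80% is tied to the pre-to-post exercise effect in earlier work that the article itself describes as done in obese men. The hypothesis is a prednisolone-placebo difference after exercise in men with BMI 19 to 27. For insulin sensitivity, the effect used for planning is not estimated in this trial at all.

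The true power is unknown. For the ucOC change, the illustration runs from 17% (half the rise removed, ρ = 0) to 98% (all of it removed, ρ = 0.75), and direct suppression could raise it further. That range rests on a two-sided paired t-test, on 80% power being right for the exercise effect, and on equal variability on the two days. No corresponding figure can be given for insulin sensitivity.

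**What to change.** Keep 12 participants and replace the power sentence with wording such as: *12 participants completing both trials give 80% power (two-sided alpha 0.05, paired t-test) to detect a prednisolone-placebo difference of 0.89 SD of the within-participant difference, for each primary outcome separately.* Stop presenting the 6.5% and 35% exercise effects as the basis for the 80%; they can remain as background, with the source population named.

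The restated sentence does not show that 0.89 SD is a realistic effect. If the sponsor holds an expected prednisolone-placebo difference and a paired SD for each primary outcome, the article should give the power at n = 12 from those.

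The cost is one paragraph and no added participants. The drawback for the sponsor is that the stated figure becomes less favourable: a detectable effect in SD units in place of an unqualified 80%.
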